#### Neuropsychological assessments

Several neuropsychological assessments will be conducted via a self-written (by YS) HTML-/JavaScript-based app. The Implicit Association Task [47] measures the association bias. Participants sort smoking-related images, images of furniture, approach words, and avoidance words using a left and right key. Smoking approach associations are measured as the extent to which participants respond more quickly in trials in which smoking-related images are paired with approach words. The Kirby Delay Discounting Task [48] measures the delay discounting rate, which reflects the degree to which the value of an outcome decreases in the future. A lower discounting rate means that a person places a greater value on future consequences, which is associated with higher self-control. The task contains 27 trials, and in each trial the participant makes a choice between a smaller, immediate amount and a larger, delayed amount. The Iowa Gambling Task [49] measures decision-making, which is related to the processing of rewards. Participants are presented with four decks of cards. They can win or lose game money by selecting cards one at a time and learn over time that different decks entail different levels of risk and reward.

#### Questionnaires

Please see Table 1 for a description of the questionnaires applied throughout the study.

### Second investigation day (T2)

The second investigation day (T2) takes place after the six-week intervention period. Parallel to T1, participants will complete several fMRI tasks, neuropsychological assessments, and questionnaires. An overview and schedule of all measurements conducted in the study is provided in Table 1.

### Follow-up (T3)

Three months after the second investigation day, participants will be invited to a follow-up (T3). The same assessment as for the second investigation day will be administered, excluding fMRI. Cotinine, an established marker of tobacco smoke absorption, will be assessed from hair samples to assess nicotine intake during the last weeks. If the participants are not able or not willing to conduct the visit in person, a telephone follow-up will be suggested. This will allow to record instances of relapse and rates of nicotine consumption, but without neuropsychological testing. A detailed overview of the information collected at the specific time points is shown in Additional file 1.

### Statistical analyses

Overall, we aim to examine the effect of different training conditions on the imbalance between habitual and goal-directed behavior in individuals with TUD. Thus, different aspects of this question (e.g., reward devaluation, PIT-effect, cue-reactivity, neuropsychological functioning, and smoking behavior) will be analyzed and results will be integrated on a conceptual level.

Primary outcome measures include (1) change in the imbalance between goal-directed and habitual behavior using the reward devaluation fMRI paradigm; (2) change in implicit smoking-related associations using an implicit association task; (3) change in attentional bias to smoking using a dot-probe task; (4) change in smoking urges using the questionnaire of smoking urges; (5) change in working memory capacity using a spatial working memory task; (6) change in planning ability using the One Touch stockings of Cambridge task; (7) change in cognitive flexibility using the Internal–External Set Shifting task. Secondary outcome measures include (1) nicotine consumption level; (2) neural PIT effect; (3) neural cure-reactivity.

Pre-processing and statistical analyses of brain imaging data will be performed using SPM12 (Wellcome Centre for Human Neuroimaging at University College London, London, UK). After pre-processing, including motion correction, normalization to the Montreal Neurological Institute (MNI) template, and a spatial smoothing with Gaussian kernel of 8 mm full width at half maximum (FWHM), the images will be analyzed using the general linear model (GLM) approach at the first (single subject) and second (group) level. Regarding the reward devaluation fMRI task, the first level contrasts “cigarette versus chocolate” for the extinction phase and “cigarette versus chocolate versus no cue” for the PIT phase will be used for subsequent group analyses. The contrast “2-back versus 0-back” will be used for the 2-back fMRI task, and “tobacco versus neutral” (and also comparisons of the different smoking contexts) will be used for the cue reactivity fMRI task. To analyze the effect of the group (3 treatment conditions) and time-point (T1, T2), we will use a factorial 3 × 2 design on the behavioral and neural levels. Correction for multiple statistical testing will be done applying a family-wise error (FWE) correction at a level of *p* < 0.05. Further, t-tests and regression analyses will be conducted, e.g., to assess group differences at baseline that possibly need to be accounted for in subsequent analyses. Additional repeated measures analyses will be conducted to integrate data from T3 (follow-up) in order to assess the effect of group on abstinence and/or substance consumption.

In a second, exploratory and data-driven approach, we will use representational similarity analysis (RSA, [50]). With RSA, latent brain representations of psychological constructs can be examined not only across conditions and studies, but also between subgroups of individuals. In this study, we are using RSA to identify subgroups of smokers that might differ in biobehavioral activation patterns by exploring latent brain representations of goal-directed versus habitual behavior using above-described fMRI tasks.

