### Sample size

Sample size estimation was conducted using the software package G*Power http://www.gpower.hhu.de), focussing on neurobiological correlates of changes in goal-directed and habitual smoking behaviour following the interventions. Expecting a minimum effect size of f = 0.2 (repeated measures design with within- and between subject factors and interactions), 28 participants per group (SCP, SCP + CRT, SCP + ICHT) will be needed to obtain at least 90% power for our main analyses at 5% alphas level. To counteract possible dropouts, 30 participants per group will be included.

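### Seven equal-ranking primary outcomes, with a multiplicity correction whose family is undefined: either the primary error rate is about 18–30%, or the stated 90% power does not hold per outcome

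*Protocol article*

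**What the plan says.** All references are to the Methods of the protocol article.

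- **Statistical analyses, outcomes.** The list begins "Primary outcome measures include (1) change in the imbalance between goal-directed and habitual behavior using the reward devaluation fMRI paradigm" and ends with "7) change in cognitive flexibility using the Internal–External Set Shifting task". Between these come implicit associations, attentional bias, smoking urges, spatial working memory and planning. All seven have the same status. The different aspects of the question "will be analyzed and results will be integrated on a conceptual level".
- **Statistical analyses, imaging paragraph.** "Correction for multiple statistical testing will be done applying a family-wise error (FWE) correction at a level of" p < 0.05. The paragraph opens with SPM12 pre-processing and goes on to first-level contrasts. The sentence itself directly follows the one that sets a 3 × 2 (group by time point) design for both behavioural and neural data.
- **Sample size.** The calculation is described as "focussing on neurobiological correlates of changes in goal-directed and habitual smoking behaviour following the interventions". It is specified by "Expecting a minimum effect size of f = 0.2 (repeated measures design with within- and between subject factors and interactions", and the result is "28 participants per group (SCP, SCP + CRT, SCP + ICHT) will be needed to obtain at least 90% power". The level is given in "at least 90% power for our main analyses at 5% alphas level".

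**The concern.** Seven outcomes carry the label primary, but the article does not say whether one significant result, a particular one, or a pattern would support the hypotheses. If each is tested at 5%, the chance of some significant primary result by luck is well above 5%.

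The risk is concrete here because the Objectives give the two add-on arms different mechanisms: cognitive control for the chess-based training, and early processing and emotional valence for the habit training. Outcomes (5) to (7) plausibly belong to the first mechanism and (2) to the second, although the article does not assign them. Three independent uncorrected tests already carry 1 − 0.95³ = 14.3%, so an isolated chance finding could be presented as confirming one mechanism.

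The stated FWE correction does not settle the matter, because what it covers is not stated. The sample size was also calculated as if there were one test at the full 5%.

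**Working it through.** **1. Reproduce the stated sample size.** Inputs from Sample size: f = 0.2, α = 0.05, power at least 90%, 28 per group (N = 84). From Statistical analyses: 3 groups and m = 2 time points. The article gives no repeated-measures correlation, so ρ = 0.5 is an assumption (the G*Power default).

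For the group-by-time interaction, λ = f²·N·m/(1 − ρ), with degrees of freedom 2 and N − 3.

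- N = 84: λ = 0.04 × 84 × 2 / 0.5 = 13.44, power 90.7%.
- N = 81: power 89.5%.

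So 84 is the smallest equal-group total that reaches 90%, and the stated figure is reproduced as one interaction test at an unsplit 5%. With ρ = 0.3 the requirement would be 114, and with ρ = 0.7 it would be 51, so 0.5 is very likely the value used.

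**2. Reading A: the FWE correction works within image maps only.** A within-map correction makes outcome (1) a single 5% test. The other six are then also tested at 5% each. With all seven null hypotheses true and the outcomes independent:

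1 − 0.95⁷ = 0.302.

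For a common correlation r between outcomes, with c = 1.96:

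error = 1 − ∫ φ(t) [Φ((c − √r·t)/√(1 − r)) − Φ((−c − √r·t)/√(1 − r))]⁷ dt.

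This was checked against 20,000 simulated trials of seven three-group F tests with 28 per group. The article gives no correlations, so r is varied:

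| r | Formula | Simulated F tests |
|---|---|---|
| 0 | 30.2% | 29.8% |
| 0.3 | 27.2% | 27.3% |
| 0.5 | 23.0% | 23.7% |
| 0.7 | 17.8% | 18.7% |

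**3. Reading B: the FWE correction spans the seven outcomes.** The error rate is then at most 5%, but each outcome must first pass 0.05/7 = 0.00714 (Bonferroni, which is also Holm's first step). With f = 0.2 and ρ = 0.5 as in step 1:

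- N = 84: λ = 13.44, power 71.3% (against 90.7% at 5%).
- N = 90: λ = 14.4, power 75.6% (against 92.6% at 5%).
- 90% power at this threshold needs N = 120, or 40 per group.

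Neither reading gives both a 5% error rate across the seven primary outcomes and 90% power for each.

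**The case against.** The strongest reply is that a correction is stated. The sentence is worded generally, names neither voxels nor maps, and follows a sentence covering both behavioural and neural data. A reader might infer from the list of seven that nothing at all is corrected, but the text does not support that as fact. This part of the reply stands: the defect is an undefined family, and the 18–30% applies only if the family excludes the seven outcomes. The reply does not clear the plan, because the other reading contradicts the stated power.

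A second reply is that a condensed article leaves such detail to the analysis plan. That would answer a complaint about silence. Here the article itself fixes seven primary outcomes, an unsplit 5%, a sample size for one test and a correction sentence, and these do not fit together.

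A third reply is that the study aims at mechanisms rather than general efficacy, as Study population and design says, and that the arm-specific hypotheses limit interpretation. This softens the point. However, the Discussion speaks of superiority testing, and only the representational similarity analysis is labelled exploratory.

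**Conclusion.** The point holds in conditional form. On the likelier reading (correction within imaging maps), the chance of at least one false-positive primary result is about 30% with independent outcomes, 23% at a correlation of 0.5 and 18% at 0.7. This assumes one 5% test per outcome and all seven nulls true; the correlations are assumed. On the alternative reading, error is controlled but power per outcome is about 71% (84 participants) to 76% (90), given f = 0.2 and an assumed ρ of 0.5.

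A reader might also count three pairwise arm comparisons per outcome and arrive at 1 − 0.95²¹, about 66%. The article does not support that figure. It specifies a 3 × 2 factorial analysis, not 21 separate primary tests, and pairwise contrasts among three arms share data and so are not independent.

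**What to change.** Make one of two changes before outcome data are examined, and record it as a dated change in the protocol, the analysis plan and the registry entry.

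- **(a) Keep seven primary outcomes.** Apply Holm across the seven group-by-time tests, and restate power per outcome as about 71–76% at the first Holm step (f = 0.2, ρ = 0.5). Later Holm steps use looser thresholds, so this is the least favourable step. The cost is lower power per outcome; restoring 90% at that step would take 120 participants instead of 90.
- **(b) Name a single primary outcome.** Choose one pre-specified scalar from outcome (1), tested at 5%, and make outcomes (2) to (7) secondary with Holm across the six. This keeps the present sample size and is consistent with its neurobiological focus, although the Sample size section does not single out outcome (1). The cost is that the outcomes closest to the arm-specific hypotheses lose primary status.

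In both cases, state that the voxelwise FWE correction is a separate correction within each image map.

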On a neural level, goal-directed behavior has been associated with prefrontal cognitive control mechanisms, whereas habitual behavior seems to be mainly controlled by shifts from mesolimbic to dorsal striatal pathways [4, 7]. Thus, the imbalance between goal-directed and habitual behavior in addiction is associated with a dysfunction of fronto-striatal circuits [8, 9]. Frontal control mechanisms involve, among other brain regions, the dorsolateral prefrontal cortex (DLPFC) and the inferior frontal gyrus (IFG) [10]. While goal-directed behaviour depends on a cortico-striatal network, the rigid stimulus–response habit system recruits a striato-nigro-striatal dopamine-dependent loop circuit. The shift of these two networks should not be considered in isolation but instead be integrated into a broader striatal dynamics model based on a shift from ventral to dorsal striatum [11]. In fact, there is evidence from human studies on alcohol of a shift from ventral to dorsal striatal responses, involving a change from hedonic to compulsive drug use [12]. Further, Pavlovian-to-instrumental transfer (PIT) paradigms have shown that originally acquired appetitive Pavlovian associations can be transferred to instrumental responding and can override unfavorable instrumental responses and, vice versa, negative Pavlovian associations can induce unfavorable behavioral inhibition [13]. In the case of substance use disorder (SUD), it has been shown that PIT effects are enhanced in individuals with alcohol use disorder and that the PIT effect was associated with increased striatal activation, which was predictive of the amount of alcohol intake and relapse [14]. To what extent these psychobiological changes also play a role in tobacco use disorder is controversial [15]. Further, it is still unclear whether subgroups of individuals with TUD with different motivational foci might be identifiable—ultimately resulting in individually different treatment needs.

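### The 90% power claimed for neural change belongs to one scalar test at 5%, not to the FWE-corrected map test in the analysis section

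*Protocol article*

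**What the plan says.** **Sizing (Protocol article, Sample size).** The calculation is described as "focussing on neurobiological correlates of changes in goal-directed and habitual smoking behaviour following the interventions". Its inputs are "Expecting a minimum effect size of f = 0.2" in a "repeated measures design with within- and between subject factors and interactions". It concludes that "28 participants per group" give "at least 90% power for our main analyses at 5% alphas level". Thirty per group are to be enrolled to cover dropout.

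**Neural test (Protocol article, Statistical analyses).** Primary outcome 1 is the change in imbalance measured with the reward devaluation fMRI paradigm. Images are smoothed at 8 mm and analysed in SPM12. The cigarette-versus-chocolate contrast of the extinction phase is carried to group level, where a 3 × 2 (group by T1/T2) design is used for both behavioural and neural data. On multiplicity the section says: "Correction for multiple statistical testing will be done applying a family-wise error (FWE) correction at a level of" p < 0.05. It gives no region, mask or search volume, and does not say whether inference is at voxel or cluster level.

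**Circuit (Protocol article, Background).** The text does name candidate regions: "Frontal control mechanisms involve, among other brain regions, the dorsolateral prefrontal cortex (DLPFC) and the inferior frontal gyrus (IFG"), and for the striatum "a shift from ventral to dorsal striatum". The analysis section does not use them.

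**The concern.** The sample size is justified by neural change, so a reader will take the 90% as the power of the neural test of primary outcome 1. But the sizing uses one test at 5%, while the analysis applies FWE correction to a map. These tests have very different thresholds. If the map test is much weaker than the one that was sized, a real effect of the planned size could fail the threshold. The null map would then be read as absence of neural change, with a 90% power claim apparently behind it. The Background already supplies regions that would support a test close to the one that was sized.

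**Working it through.** **Inputs from the article:** f = 0.2; 3 groups; 2 time points (T1, T2); 28 per group, so N = 84 (90 enrolled); α = 0.05; power at least 90%.
**Assumed:** T1–T2 correlation ρ, which the article does not give; sphericity, which is automatic with two time points; search volume 1,200–1,500 cc; effective smoothness 8–15 mm (the planned kernel is 8 mm).

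**Step 1. Reproduce the 28 per group.** For the within-between interaction with m = 2 time points, λ = f²·N·m/(1 − ρ), with df 2 and N − 3. At ρ = 0.5:

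λ = 0.04 × 84 × 2 / 0.5 = 13.44; F(2, 81) critical value at 5% = 3.11; power = 90.7%.

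The smallest balanced N reaching 90% is exactly 84. The other variants tried do not give 84: within-subject main effect 69, between-subject effect 243, λ without the correlation term 162, three time points 69, ρ = 0.3 gives 114, ρ = 0.7 gives 51. The planning model is therefore taken as one scalar interaction test at 5% with ρ = 0.5.

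**Step 2. Threshold under whole-brain voxel-level FWE 0.05.** Random-field theory for an F(2, 81) field: solve Σ (resels_d × EC density_d) = 0.05, treating the search volume as a sphere.

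- 1,500 cc at 8 mm: 1,500,000/8³ ≈ 2,930 resels; F = 18.3; voxelwise p ≈ 3 × 10⁻⁷
- 1,200 cc at 15 mm: 1,200,000/15³ ≈ 356 resels; F = 14.9; voxelwise p ≈ 3 × 10⁻⁶

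The planned test needs F = 3.11.

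**Step 3. Power at a given voxel with f = 0.2, N = 84.**

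| ρ | λ | Scalar test at 5% | Whole-brain voxel-level FWE |
|---|---|---|---|
| 0.5 | 13.44 | 90.7% | 2–6% |
| 0.75 | 26.88 | 99.7% | 25–44% |
| 0.80 | 33.60 | >99.9% | 45–66% |

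With all 90 participants retained and ρ = 0.5, the last column is 3–8%. At ρ = 0.75 or 0.80 the scalar plan would have needed only 45 or 36 participants in total, so those values do not fit the stated 28 per group. They are shown for range.

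**Step 4. Region-mean tests, ρ = 0.5, Bonferroni level.**

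| Regions | α per region | Power, N = 84 | Power, N = 90 | N for 90% |
|---|---|---|---|---|
| 1 | 0.05 | 90.7% | 92.6% | 84 |
| 2 | 0.025 | 84.8% | 87.7% | 96 |
| 4 | 0.0125 | 77.7% | 81.4% | 111 |

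This assumes that the region mean carries the same f as the voxel.

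**Step 5. Voxelwise search inside a small volume.** For 1–20 cc at the same smoothness range, power at a given voxel is about 17–64% (N = 84, ρ = 0.5). This is not equivalent to a region mean.

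**The case against.** The best defence is that this is a condensed article. Masks, small-volume correction and the level of inference commonly sit in a full protocol or SAP that is not shown, so their absence alone is no fault. That stands. The point rests instead on two things the article does state: a power figure for neural change at one 5% test, and an FWE-corrected map analysis. Masks held elsewhere would not make the published power figure refer to a map test.

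A reader might infer that an effect of the planned size would almost surely be missed. The article does not support that. It requires whole-brain search, voxel-level inference and ρ = 0.5 all at once. The article mentions whole-brain coverage only for image acquisition, does not state the level of inference and gives no correlation. Higher correlations raise the power at a voxel to 25–66%. Cluster-level inference would do better still, and after 8 mm smoothing a regional effect spans many voxels, any of which may pass.

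A reader might also infer that primary outcome 1 has no usable summary, or that any surviving cluster could be called a changed imbalance. The Reward devaluation paragraph gives a behavioural readout, choice in the extinction phase, which voxelwise FWE does not touch. For the maps, the extinction contrast is fixed and FWE limits false positives.

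Finally, the Background's list of frontal regions is openly non-exhaustive, and no passage predicts a striatal effect for ICHT specifically. Neither a mandatory four-region circuit nor a per-arm regional prediction can be drawn from the text.

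**Conclusion.** The mismatch holds. The 90% describes one scalar group-by-time test, while the neural test as stated is FWE-corrected over a map with no region named. The power of that neural test is unknown from the article. On the natural reading it is far below 90% for a given voxel across the correlations examined, with the low figures in Step 3 conditional on voxel-level inference and on the assumed search volume and smoothness. A region-mean test recovers the planned power fully for one region and most of it for two or four. The behavioural analysis of the same paradigm is outside this point. It should be changed, but it does not show that the trial cannot detect neural change.

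**What to change.** In Statistical analyses, define the neural test of primary outcome 1 as the group × time effect on the mean cigarette-versus-chocolate estimate (extinction phase) in a small set of anatomical regions. Draw these from the Background's circuit and fix them before the group maps are seen: for example one frontal and one striatal mask, or DLPFC, IFG, ventral striatum and dorsal striatum. Apply Holm correction across the regions at 5%, and report whole-brain FWE maps as exploratory. Do not substitute a voxelwise small-volume search for the region mean.

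In Sample size, restate the power for the chosen test, with the correlation given. At N = 84 and ρ = 0.5 it is about 91%, 85% or 78% for one, two or four regions at the Bonferroni level; Holm is never less powerful than that.

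The change is to wording and analysis only; no new scans are needed. It has three costs. Effects outside the masks become exploratory. A mask mean can dilute a focal effect. With more than one region the power falls below the stated 90% unless the sample grows (96 in total for two regions, 111 for four).

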### Study population and design

The sample will comprise 90 right-handed, treatment-seeking smokers (males and females) between 18 and 65 years of age, who will attend a 6-week program for smoking cessation. Recruitment will take place using public advertisement, newspaper articles or web-based public calls for participation. Eligibility criteria include at least four of eleven TUD criteria according to DSM-5, sufficient ability to communicate with investigators and answer oral and written questions and ability to provide written fully informed consent. Individuals will be excluded, if they meet any of the following criteria: severe internal, neurological, and/or psychiatric comorbidities, axis I mental disorders other than TUD according to the International Classification of Diseases (ICD-10) and DSM 5 (except for mild depression, adaptation disorder and specific phobias) in the last 12 months, history of brain injury, severe physical diseases, common exclusion criteria for MRI (e.g., metal, claustrophobia), positive drug screening (opioids, benzodiazepines, barbiturates, cocaine, amphetamines), psychotropic medication within the last 14 days and pregnancy.

90 participants will be randomized into three groups (3 × 30 smokers): Standard smoking cessation program (SCP), standard SCP plus CRT and standard SCP plus ICHT. In addition to the screening for suitability to participate in the study, three investigation days per subject are planned. Participants will be assessed before SCP (Baseline, T1), after a 6-week smoking SCP (T2), and in a detailed follow-up after three months (T3). The comparison will be limited to SCP rather than an additional placebo control group, since the study aims to analyse treatment-related mechanisms rather than general efficacy. See Fig. 1 for more details.

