## Discussion

Major detrimental health consequence of smoking and high relapse rates in individuals with TUD underline the still highly relevant need for further understanding of the disorder, i.e. neurobiological and behavioral mechanisms, and its treatment. With the present study project, we aim to contribute to this research gap by examining the effect of different therapeutic interventions on the imbalance of habitual and goal-directed behavior. We expect an imbalance between goal-directed and habitual behavior in treatment-seeking smokers, on the behavioral as well as on the neural level. Further a differential modification of this imbalance and its neural correlates is hypothesized when comparing SCP + CRT, SCP + ICHT and standard SCP. In addition, we expect a prediction of relapse by the imbalance between goal-directed and habitual behavior.

Of particular interest, not only for our study participants but the research community as well, we combine superiority testing of therapy modules with basic research on different levels (neurobiological, behavioral and psychological) and thus contribute to broadening the understanding of this complex disorder. As a major highlight, we postulate a positive effect of therapy add-ons on smoking behavior and abstinence rates due do adaptations und underlying neurobiological functioning. Further, we propose an additional, beneficial effect of our approach with regard to individualized medical interventions. If individual mechanisms of TUD prove to be identifiable, efficacious treatment options under study condition, e.g., cognitive versus habit training, might be administered more efficiently with respect to the individual’s needs—and hopefully prove to be equally effective in the naturalistic setting. Applying our proposed cognitive and computer-based habit training in groups further highlights the efficiency of these therapy add-ons. The repeated measures design can be considered a methodological strength as reduced error variance results from each participant being its own control [51].

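### Adjustment for the T1 value should be fixed in advance: the planned 3 × 2 analysis of change, adjusted only if baseline differences appear, is valid but gives up precision

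*Protocol article*

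**What the plan says.** In the protocol article, Statistical analyses, the effect of group (three arms) and time point (T1, T2) is to be examined as follows: "we will use a factorial 3 × 2 design on the behavioral and neural levels". The seven primary outcomes in the same section are all worded as changes. Further t-tests and regressions are announced, with one example of their purpose: "to assess group differences at baseline that possibly need to be accounted for in subsequent analyses". The section gives no rule for when a difference counts, which variables are meant, or how they would enter the model.

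The Sample size section reads "Expecting a minimum effect size of f = 0.2 (repeated measures design with within- and between subject factors and interactions" and says that 28 per group "will be needed to obtain at least 90% power for our main analyses" "at 5% alphas level". It then adds: "To counteract possible dropouts, 30 participants per group will be included". The Discussion comments on the design: "The repeated measures design can be considered a methodological strength as reduced error variance results from each participant being its own control".

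Two other places bear on the point. The Baseline assessment (T1) section lists group allocation among the steps that precede T1. The task descriptions quote retest reliabilities above 0.75 for cue reactivity (a secondary outcome) and 0.90 for the N-back task (not a listed outcome).

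**The concern.** With two time points, the group-by-time interaction in a 3 × 2 design is the one-way comparison of T2 − T1 change between arms. Subtracting T1 applies a slope of 1 to the baseline. Regression on T1 estimates the slope from the data, which cannot do worse in large samples and does better when the T1–T2 correlation is moderate.

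The only adjustment mentioned depends on what is seen at baseline. In a randomised comparison such tests are a poor trigger, because an imbalance far from significance can still shift the arm contrast. What is at stake is precision that the T1 measurements could already supply, protection against chance imbalance at T1, and a final model that does not depend on choices made after seeing the data across seven primary outcomes.

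**Working it through.** **Inputs.** From the article: three groups, 28 per group needed (84 in total), 30 per group randomised, f = 0.2, alpha 0.05, target power 90%. Assumed: equal variances at T1 and T2, and the correlation rho, which the article does not state.

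**Step 1: the plan's own figure.** For the within-between interaction with k = 3 groups and m = 2 time points, lambda = f² × N × m / (1 − rho), with df k − 1 and N − k. At rho = 0.5, lambda = 0.04 × 84 × 2 / 0.5 = 13.44 with df 2 and 81. Power is 0.907, and 84 is the smallest balanced total that reaches 90%. The stated 28 per group is therefore reproduced. Rho 0.5 is not the only route: with three time points, rho of about 0.375 also gives 84. It remains an assumption.

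**Step 2: variance.** In units of the single-visit variance:
- change: 2(1 − rho)
- T2 adjusted for T1: 1 − rho²
- ratio, adjusted to change: (1 − rho²) / [2(1 − rho)] = (1 + rho)/2

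Since 2(1 − rho) is below 1 only when rho exceeds 0.5, change scores are no more precise than T2 alone at rho 0.5. The Discussion's remark on reduced error variance is a general one and depends on rho in this way.

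**Step 3: power at f = 0.2.** The adjusted analysis divides lambda by (1 + rho)/2 and spends one residual df. At rho 0.5, lambda = 13.44 / 0.75 = 17.92 with df 2 and 80.

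| rho | variance saving | power at 84, change | power at 84, adjusted | total N for 90%, change | total N for 90%, adjusted |
|---|---|---|---|---|---|
| 0.3 | 35% | 0.783 | 0.932 | 114 | 78 |
| 0.5 | 25% | 0.907 | 0.969 | 84 | 63 |
| 0.75 | 12.5% | 0.997 | 0.999 | 45 | 39 |
| 0.9 | 5% | 1.000 | 1.000 | 21 | 21 |

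**Step 4: what a baseline test recovers.** The article states no rule, so one was assumed: adjust for T1 only if the overall baseline F test has p < 0.05. The simulation used 20,000 trials of 3 × 28 at rho 0.5 with no treatment effect.

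| | change | test, then adjust | always adjust |
|---|---|---|---|
| mean of a pairwise contrast | 0.0008 | 0.0003 | 0.0006 |
| variance of a pairwise contrast | 0.0722 | 0.0690 | 0.0549 |
| mean error (SD) at a chance T1 difference near 0.3 SD | −0.146 | −0.142 | 0.002 |
| overall type I error | 0.053 | 0.047 | 0.052 |

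Theory gives variances of 2 × 2 × 0.5 / 28 = 0.0714 for change and 2 × 0.75 / 28 = 0.0536 for adjustment, in line with the simulation. The expected error of the change contrast at a 0.3 SD imbalance is (0.5 − 1) × 0.3 = −0.15 SD. The conditional rule barely helps because it adjusted in only about 5% of trials. With 28 per group, the standard error of a baseline difference is √(2/28) = 0.267 SD, so a 0.3 SD imbalance is only 0.3 / 0.267 = 1.1 standard errors. In the trials where the baseline test was significant, type I error was 0.165 for unadjusted change and 0.058 for the adjusted analysis.

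At rho 0.75 the pattern is the same but smaller: the errors at a 0.3 SD imbalance are −0.082, −0.079 and −0.008 SD.

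**The case against.** The planned analysis is valid, and several stronger readings go beyond the documents.

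- **Bias.** A reader might infer that the change analysis is biased. Under randomisation it is not: all three estimators average about zero. The error arises only conditional on chance T1 imbalance.
- **Invalid p-values.** Data-dependent adjustment might suggest an inflated type I error. Under the simulated rule the overall rate was 0.047, so this is not supported.
- **Lost participants.** A classical repeated-measures ANOVA would drop anyone without T2, but the article names neither an estimator nor a missing-data rule. A regression of T2 on arm and T1 would drop them too.
- **A firm 25%.** This rests on rho 0.5. At the only retest values quoted, the saving is about 12.5% or less, and 5%. Neither value concerns a primary outcome, so they do not settle the matter either way.
- **Imaging.** The Sample size section focuses on neurobiological correlates, and the first primary outcome is an fMRI paradigm. The power figures above do not describe a voxelwise analysis that stays on change.
- **Wording.** The baseline tests are introduced as an example and adjustment as a possibility, and the variables need not be T1 outcome values. A separate analysis plan may fix the covariates.

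All of this limits the point. It still stands that the article fixes a change analysis and describes adjustment as contingent on observed differences, where a better use of the same data is available.

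**Conclusion.** The point holds as an efficiency and pre-specification improvement, not as a fault that invalidates the trial. Pre-specified T1 adjustment has (1 + rho)/2 times the variance of the planned change analysis, a saving of 5% to 35% for rho between 0.9 and 0.3. The gain in power is material at rho 0.3 to 0.5 and negligible at 0.75 or above. It also removes the error from chance T1 imbalance, nearly all of which the simulated baseline-test rule left in place.

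The conclusion rests on equal variances at T1 and T2, an unstated rho, an assumed form of the conditional rule, and a T1 value that allocation cannot have influenced. The last is not secured, because the article places T1 after group allocation. It does not say whether participants know their arm by then. If they do, self-reported measures such as smoking urges could already differ by arm. Equality at T1, on which a baseline-constrained model relies in particular, could then not be taken for granted.

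**What to change.** 1. For each behavioural primary outcome, and any region-mean neural outcome, model T2 on arm with the T1 value of that outcome as a fixed covariate, named in advance. Alternatively, use a baseline-constrained mixed model. The two are related but not identical, and the mixed model keeps participants without T2.
2. Remove baseline tests as a trigger for adjustment, and describe baseline characteristics by arm without p-values.
3. Leave the voxelwise SPM analysis as planned, and do not claim the precision gain for it.
4. State the T1–T2 correlation assumed in the sample size calculation.
5. Ensure, and state, that T1 is measured before participants learn their arm.

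Items 1 to 4 cost wording and one residual degree of freedom per model, with no new data. Item 5 may affect the order of visit procedures if T1 currently follows disclosure of the arm.
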